### Outcome measures

A proposed schedule for enrolment, intervention, and assessment is shown in the Standard Protocol Items: Recommendations for Interventional Trials (SPIRIT), Table 1. In addition, recommended items to address for intervention trials are reflected in the SPIRIT Checklist [38] (Additional file 1) and in the WHO Trial Registration Data set (Additional file 2).

**Table 1 Tab1:** Standard Protocol Items: Recommendations for Interventional Trials (SPIRIT) figure: proposed schedule for enrolment, intervention, and assessment

Time point		Study period					
	Enrolment	Stabilization phase	Allocation	Post-allocation			Close-out
	***t***_***1***_	***t***_***2***_	***t***_***3***_	***t***_***3***_	***t***_***4***_	***t***_***5***_	***t***_***5***_
**Enrolment**							
**Eligibility screen**	X						
**Informed consent**	X						
**Medical screening**			x				
**Nutrition check**	x	x			x		
**Allocation**			x				
**Interventions***							
***[EXEPROT]***				↔	↔	↔	
***[PROT]***				↔	↔	↔	
***[REC]***					x	x	
**Assessments**							
***[Baseline variables, gender, age, education, marital status, depression, incontinence, chronic diseases, use of medication, risk of poor protein intake, eating symptom questionnaire, risk of dysphagia, appetite, dental status]***				X			
***[primary outcome variable lower leg muscle power]***				x		x	X
***[secondary outcome variables physical frailty status, jump muscle power, leg press, hand grip strength, SPPB, waist and hip circumference, body weight, lean mass, fat mass, BMD, health-related QoL, pain, fatigue, ADL, fear of falling, blood markers, physical activity, sedentary behavior, nap and sleep, dietary intake, walking speed, rising from laying position, MNA, EVS, risk of poor protein intake, DDST]***				x		x	x

*DSST* Digit Symbol Substitution Test, *SPPB* Short Physical Performance Battery, *BMD* bone mineral density, *QoL* quality of life, *ADL* activities of daily living, *MNA* Mini Nutritional Assessment, *EVS* Eating Validation Scheme

*See explanation in the text

#### Test sessions

Five test sessions will be performed (T1–T5), see Fig. 1 and Table 1.

T1, T2 and T4: The pre- and post-test of the stabilization period and the test halfway through the intervention will consist of a nutrition check including assessment of protein intake by Pro 55+, 4-day food records, and 24-h recall interviews.

T3 and T5: The pre- and post-intervention test will include assessment of baseline variables and primary and secondary outcomes (specified in Table 2).

**Table 2 Tab2:** An overview of variables and outcomes, outcome measures, instruments and time point for the assessment

Outcome	Outcome measures	Instrument	Time point
**Descriptive variables**			
Personal information	Age, gender, former job, marital status, educational background and chronic diseases	Self-report	T3
	Depression	The Major Depression Inventory (MDI) [39]	T3
	Incontinence	International Consultation on Incontinence Questionnaire (ICIQ) [40]	T3
	Eating ability	Self-reported dental state	T3
		The Eating Symptom Questionnaire [41]	
		The EAT-10 Questionnaire [42]	
		Simplified Nutritional Appetite Questionnaire [43]	
**Primary outcome**			
Muscle power	Lower leg muscle power	The Nottingham Leg Rig [44–46]	T3 and T5
**Secondary outcomes**			
Muscle mechanical function	Countermovement jump	The countermovement jump is performed on a force platform (Kistler 9281 B, 40 × 60 × 5 cm) following the procedure described in [47]. Four maximal jumps will be performed with 1-min interval and the highest jump recorded	T3 and T5
Maximal muscle strength	Leg press	Assessed on the dominant leg in a custom-built unilateral leg press device with a fixed footplate instrumented with piezoelectric force transducers (Kistler 9367/8 B). The force signals will be digitally sampled at 1 kHz while on-line visual feedback is provided to the subject. The contractile rate of force development and impulse will be determined in the trial with the highest resultant peak force [44, 48]	T3 and T5
	Handgrip strength	Handgrip strength is measured using a handheld dynamometer (Original Smedley’s Daynameter, Scandidact, 100 kg, Cat. No. 281128). Participants are instructed to sit with the elbow at a 90° angle, the wrist in neutral position. The inner lever of the dynamometer is adjusted to the hand of the participants (the second phalanxes against the lever) (Andersen-Ranberg et al. 2009). A minimum of three contractions in each hand will be performed and testing continues until participant produce less force than the prior test.	T3 and T5
Physical Frailty Status	The SHARE-FI75+ Fried frailty phenotype	The SHARE-FI75+ is a physical frailty assessment tool that is developed specifically for community-dwelling adults aged ≥ 75 years [5]	T3 and T5
		Fried frailty phenotype consists of five variables where three are based on questions: (i) unintentional weight loss, (ii) self-reported exhaustion, and (iii) low energy expenditure and the remaining two are based on objective assessment: (iv) slow gait speed and (v) weak hand grip strength [9]. The variable ‘low energy expenditure’ is modified to follow the current recommendations on physical activity in older adults from the World Health Organization [49].	
Risk of malnutrition	Protein intake	The Protein Screener Pro55+ is used to assess the risk of poor protein intake [35]	T1, T2, T3 and T5
		Four days food records (filled out on three weekdays and one day during the weekend) are calculated (Winfood 4.1) to estimate the average protein intake (g) per kg body weight per day and protein content per meal. In addition, energy intake and distribution of macronutrients are calculated.	
	Weight loss	Self-reported unintentional weight changes during the last month	T1, T2, T3, T4, and T5
	Nutritional status	The Eating Validation Scheme (EVS) is composed of five questions about dietary intake and weight loss and three questions about risk factors (dysphagia, eating assistance, and acute illness) [50]	T3 and T5
		The Mini Nutritional Assessment (MNA) is composed of 18 questions and measurements concerning appetite, eating ability, weight, need for help, illness, and medication [51]	
Anthropometry	Weight	Measured in light clothes, without shoes and subtracting 0.5 kg for the weight of clothes using a calibrated TANITA scale (model DC430SMA)	T3 and T5
	Waist- and Hip- circumference	Following the protocol by the World Health Organization [52]	
	Height	Measured without shoes	T3
Body composition	Estimation of fat mass, fat-free mass and bone mass	Dual-energy X-ray absorptiometry (DXA) (Lunar Prodigy) scans will be used to assess whole body composition with special emphasis on lean mass and fat tissue as well as bone mineral density.	T3 and T5
		Foot-to-foot bioelectrical impedance analysis (BIA), using the TANITA Total Body Composition Analyzer (model DC430SMA).	
Physical function and mobility	Gait speed, Chair stand, Balance	The Short Physical Performance Battery (SPPB) [53]	T3 and T5
		Rising from laying position on the floor and stand and reach test [54]	
		Self-selected and maximal gait speed (10 m) [55–57]	
		Distance walked during 2 min [58, 59]	
Physical activity level	Objective measures of intensity, duration, and patterns of physical activity and sedentary behavior	Hip-worn accelerometers, ActiGraph (removed during sleep)	T3 and T5
		Thigh-worn accelerometers, Axivity (24 h/day)	
		Data will be continuously collected in a raw format at 30/50 Hz, respectively, over a period of 7 days.	
	Self-reported sedentary behavior	The Sedentary Behavior Questionnaire (SBQ) [60]	T3 and T5
Activities of daily living	Self-report	Questionnaire that combines items from the Most Efficient Lists and the Short-Form of Late-Life Function and Disability Instrument [61–63]	T3 and T5
Pain, fatigue, and fatigability	Self-report	The Brief Pain Inventory - Short Form (BPI-sf) [64]	T3 and T5
		The Mobility fatigue scale “Mob-T” [65]	
		The Pittsburgh Fatigability Scale (PFS) for older adults (only the domain about physical fatigue will be assessed) [66]	
Fear of falling	Self-report	The Falls Efficacy Scale – International (FES-I) [67]	T3 and T5
		Self-reported falls within the last year	
Cognitive function	Pencil and paper test	The Digit Symbol Substitution Test (DSST) [68, 69]	T3 and T5
Health-related quality of life	Self-report	The EQ-5D-3L questionnaire [70]	T3 and T5
Biomarkers	Blood sample	Biomarkers related to nutritional status, physical activity, sedentary behavior, as well as physical and cognitive function—such as lipids, hormones, proteins, cytokines, vitamins, and minerals, e.g., cholesterol, HbA1c, adiponectin, suPAR, Crp, IL-6, B_12_ and vitamin D, vitamin B_12_ [71–74]	T3 and T5

*T1* time of enrolment, *T2* post the stabilization phase, *T3* baseline pre-intervention, *T4* half-way follow-up, *T5* close-out post-intervention

#### Data collection

Collection of data will be performed by trained research assistants from the University of Southern Denmark. Training of the research assistants includes theoretical teaching in the applied methods and tests, supervision by other research assistant, and frequent meetings with colleagues to share experiences and answers any questions that may arise. The descriptive variables (personal information, information about chronic diseases, depression, incontinence and eating ability) will be collected at baseline (T3). The primary and secondary outcomes data will be collected at baseline pre-intervention (T3) and post-intervention (T5). Participants will be invited to test irrespectively of their compliance to the intervention protocol. Participants are offered personal feedback on selected outcomes after ending the interventions to promote retention in intervention and post-intervention tests (T5).

### Primary outcome

Lower leg muscle power is the primary outcome. This will be assessed unilaterally using the Nottingham Leg Rig [44–46] on the dominant leg. A minimum of six trials will be conducted with approximately 45 s of rest between trials. Testing continues until participants produce less power than the prior test.

### Secondary outcomes

The secondary outcomes include assessment of muscle mechanical function, maximal muscle strength, physical frailty status, protein intake, risk of malnutrition, anthropometry, body composition, physical function, mobility, physical activity, sedentary behavior, pain, fatigue, fear of falling, cognitive function, health-related quality of life, and biomarkers.

For an overview of descriptive variables, outcomes, instruments, and assessment time points, see Table 2.

### Statistical analysis

Plans for data entry, coding, security, and storage including any related processes to promote data quality have been approved by the Danish Regional Data Protection Agency. The full analysis set will follow an intention-to-treat principle and will include all randomized participants. The study hypothesis will be tested with mixed linear models to assess changes in the main outcomes over time and between study arms controlling for confounders (e.g., age, sex, lifestyle factors). Per-protocol analysis of participants that are compliant to the protocol will be performed. Lastly, if sample size allows it, sub-group analysis by sex and by habitual lifestyle (protein intake and physical activity) will be performed based on baseline assessment. Wilcoxon signed rank sum test, Mann-Whitney *U* test, and odds ratio or chi-square test of relationships were used when appropriate. The statistical software programme STATA 16 (StataCorp. 2019. *Stata Statistical Software: Release 16*. College Station, TX: StataCorp LLC) will be used for the statistical analysis.

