A.An increased protein intake from dairy products combined with power training increases (i) muscle power, and (ii) muscle mechanical function, maximal muscle strength, physical function, mobility, physical activity, muscle mass, health-related quality of life, and activities of daily living (iii) decrease pain, fear of falling, sedentary behavior, risk of malnutrition and (iv) modify physical frailty status and causes and contributors associated with such status.B.Protein and power training in combination has a superior effect compared to an increased protein intake from dairy products alone and to a third intervention based on current recommendations on diet and physical activity for older adults.

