##### Phase 2: Four months randomized controlled intervention

Eligible participants will be randomized into three groups: (i) protein-only group (PROT), (ii) protein + exercise group (EXEPROT), and (iii) recommendation group (REC).
PROT intervention

The PROT group will receive protein-rich off-the-shelf dairy products with the aim of targeting a daily protein intake of 1.5 g protein/kg/day. At baseline, individual supplementation plans are made based on information about participants habitual protein intake (assessed by the food records) and taste preferences. A cutoff of 15 g of supplementary protein is used—if participants have a higher requirement for protein, there will be a stepwise increase in protein intake over the first 4 weeks. Examples of products are skimmed milk, low-fat yoghurts with a high protein content (skyr), chocolate milk, cottage cheese, and ordinary low-fat cheese. Products will be delivered once a week at the home of the participant or at the training facilities. The type of products consumed may be changed throughout the study in order to avoid sensory-specific satiety and keep the compliance high. The PROT intervention is performed by specifically trained nutritional specialists.
2.EXEPROT intervention

The EXEPROT group will receive the same protein intervention as the PROT group combined with exercise program 1 h, twice a week. The exercise is designed as power training incorporating lower and upper body exercises with a training intensity of 65–80% of 1 repetition maximum (3 sets of 10–12 repetitions), which will be progressively adjusted throughout the entire intervention. Exercises will be performed explosively (i.e., as rapid as possible) during the concentric phase of the movement and controlled during the eccentric phase. At each session, participants register exercise activities, intensity, and rate of perceived exertion. The power training is performed by specially trained exercise specialists.
3.REC intervention

The REC group will be asked to follow the European recommendations for older adults on diet and physical activity over the course of the study and will be provided with publicly available material. In addition, two seminars on specific topics related to healthy aging will be provided to the group.

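### Secondary arm comparisons may go to signed-rank, Mann-Whitney or chi-square tests, which either do not compare the arms or cannot adjust for the baseline value

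*Protocol article*

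**What the plan says.** The Statistical analysis section gives the main analysis in one sentence: "The study hypothesis will be tested with mixed linear models to assess changes in the main outcomes over time and between study arms". Per-protocol and subgroup analyses follow. The section then lists "Wilcoxon signed rank sum test, Mann-Whitney" U, and odds ratio or chi-square, ending with "test of relationships were used when appropriate". It names no outcome, comparison or trigger for these tests, and does not restrict them to comparisons outside the randomization. It names no three-group rank test and no baseline-adjusted alternative for outcomes that do not suit a linear model.

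The design is set out elsewhere in the article. Under Phase 2, "Eligible participants will be randomized into three groups". The Data collection section places the primary and secondary outcomes at T3 (before the intervention) and T5 (after it). Table 2 adds further times for two secondary outcomes: protein intake also at T1 and T2, and self-reported weight loss also at T1, T2 and T4. Aim B, at the end of the Background, is a comparison between arms: "Protein and power training in combination has a superior effect compared to an increased protein intake from dairy products alone", and also against the recommendation arm.

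**The concern.** The mixed model is assigned to the study hypothesis and the main outcomes. The secondary list is long and includes frailty category, pain, fear of falling and EQ-5D. Ordinal, skewed or categorical outcomes of this kind are the natural candidates for rank and chi-square tests, and several appear in the aims.

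For such an outcome at T3 and T5, a signed-rank test asks whether people changed. It does not ask whether arms changed differently. A significant change in one arm beside a non-significant change in another is not evidence of an arm difference. It mixes any treatment effect with practice on repeated tests, regression to the mean after selection on frailty, and chance.

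Mann-Whitney and chi-square do compare arms, but neither accepts a covariate, so the T3 value that the trial collects anyway cannot be adjusted for. The stake is twofold: a misleading reading of secondary results, and avoidable loss of power.

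**Working it through.** **1. The plan's own figure.** Inputs from Sample size determination: expected changes of 15, 0.8 and −7 (EXEPROT, PROT, REC), SD 30, power 0.8, significance level 0.05, 37 per arm, 25% dropout.
- Mean of the three changes: (15 + 0.8 − 7)/3 = 2.93. Squared deviations: 145.6 + 4.6 + 98.7 = 248.8. Divided by 3 and rooted: 9.11. Effect size f = 9.11/30 = 0.304.
- One-way ANOVA F test: 36 per arm gives power 0.802 and 37 gives 0.813. Then 37/0.75 = 49.3, rounded up to 50 per arm, or 150 in total.
- The stated size reproduces. The 37 per arm is carried forward below.

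**2. Discordant pre-post verdicts when the arms do not differ.** Let p be the chance that one arm's within-arm test is significant, the same in each arm. The chance that at least one arm but not all three is significant is 1 − p³ − (1 − p)³ = 3p(1 − p).

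Values of p are from the paired t-test (noncentral t) with 37 per arm. SD 30 is the planning SD for percentage change in muscle power, so the common change is also given in SD units for use with other outcomes.

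| Common true change | In SD units | p | 3p(1 − p) |
|---|---|---|---|
| 0 | 0 | 0.05 | 0.14 |
| 5 | 0.17 | 0.167 | 0.42 |
| 8 | 0.27 | 0.352 | 0.68 |
| 10 | 0.33 | 0.505 | 0.75 |
| 15 | 0.50 | 0.841 | 0.40 |

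A simulation of the signed-rank test itself (4,000 replicates) gave discordance of 0.14 at no change and 0.76 at a change of 10, in line with the formula. The expression 3p(1 − p) peaks at p = 0.5, where it equals 0.75, so that row is the ceiling and not a forecast.

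**3. Power lost by not adjusting for T3.** Assumptions: a true difference of 0.5 SD at T5, 37 per arm, two-sided 0.05, normal approximation, Mann-Whitney efficiency 0.955. The T3–T5 correlation ρ is not in the document; it is taken as 0.5 to 0.7. Power = Φ(δ√(m/2) − 1.96), where δ is the difference divided by the SD that applies and m is the effective number per arm.
- Mann-Whitney on T5: m = 37 × 0.955 = 35.3; 0.5 × √(35.3/2) = 2.10; power Φ(0.14) = 0.56.
- Adjusted for T3: the residual SD is √(1 − ρ²) times the raw SD. At ρ = 0.5, δ = 0.5/√0.75 = 0.577; 0.577 × √(37/2) = 2.48; power 0.70. At ρ = 0.7, δ = 0.5/√0.51 = 0.700; 0.700 × √(37/2) = 3.01; power 0.85.
- Mann-Whitney on change scores: the SD of change is √(2(1 − ρ)) times the raw SD. At ρ = 0.5 that factor is 1, so power stays at 0.56. At ρ = 0.7, δ = 0.5/√0.6 = 0.645; 0.645 × √(35.3/2) = 2.71; power 0.77.

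Change scores therefore give no gain over T5 values at ρ = 0.5, and recover about 0.22 of the 0.30 shortfall at ρ = 0.7 (0.77 against 0.85).

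**The case against.** The strongest reply is that the plan gives these tests no confirmatory role. The hypothesis goes to the mixed model, and the list of tests comes last, conditioned on being appropriate. This stands for the primary analysis: nothing here shows it to be wrong. It does not settle the secondary arm comparisons, because the section names the tests for open use and no better method for those outcomes.

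Other parts of the reply also stand:
- A reader might infer that a signed-rank test has no proper use in this trial. Table 2 does not support that. Protein intake at T1 and T2 spans the stabilization phase, which precedes randomization and has no arms, so a paired one-group test is legitimate there.
- Two-group tests have ordinary uses too, such as comparing compliant with non-compliant participants. Chi-square handles three arms directly.
- A reader might take the 75% as the expected rate of discordance. It is the mathematical maximum, and a common gain of 10 in all arms does not match the plan's own expected changes.
- A reader might charge Mann-Whitney with inflating error over three pairwise tests. Any unadjusted pairwise method does the same, so this is not an argument against it.
- A reader might think that Aim A, which names no comparator, must be reworded. Aim B, directly after it, names both comparators.

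It can also be said that a separate analysis plan may settle which outcomes take which test. That would excuse silence. Here the article names specific methods, and the objection is to their fit for randomized comparisons.

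**Conclusion.** The point holds for secondary outcomes at T3 and T5 whose arm comparison is sent to the rank or chi-square route, and for nothing wider. There, a signed-rank result is not a between-arm result, and Mann-Whitney and chi-square leave the T3 value unused.

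Reading arm effects from pre-post p-values would suggest a difference about 14% of the time with no change in any arm, and more often under a shared change. This harm arises only if within-arm tests are actually read across arms, which the document does not say will happen but does not rule out.

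The power cost at a 0.5 SD difference is 0.56 against 0.70 to 0.85 for T5-only comparisons, and less for change scores when ρ exceeds 0.5. It rests on an assumed ρ and on normal-theory figures that are only a guide for ordinal scores. The sample size and the primary mixed-model analysis are untouched. This should be changed, but it does not threaten the trial's main conclusion.

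**What to change.** In the Statistical analysis section, state that effects of arm are judged only on between-arm estimates adjusted for the T3 value, with arm as a three-level factor:
- the mixed model where it suits the outcome;
- proportional-odds or other ordinal regression for ordinal or skewed scores and frailty category;
- logistic regression for binary outcomes.

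Keep the signed-rank test for description only, for example the T1–T2 change in phase 1, and report within-arm T3–T5 changes as estimates with confidence intervals. Put the sentence listing the tests in the future tense. Aim A can stay as it is.

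The cost is one or two sentences and a little more modelling in Stata, with no new data or participants. The small downside is that the proportional-odds assumption has to be checked.

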## Discussion

This study provides a protocol for a community-based assessor-blinded RCT to determine the effects of interventions with high-protein diet alone or in combination with power training on muscle mechanical function (muscle power and strength), frailty status, functional performance, muscle mass, and quality of life. This may ultimately have an impact on the ability of older pre-frail and frail adults to maintain self-reliance for longer.

Currently, only few of the studies that have investigated the effect of combining protein and exercise have used individually assigned supplementation plans that take the participants’ habitual protein intake and preferences into account. Specifically, in relation to pre-frail or frail older adults, most former multidomain studies have focused on increasing intake of protein by means of supplements (protein powder or oral nutritional supplements) without individual adjustments in doses. In addition, several studies have been designed with resistance training protocol, but only few studies have used power training combining heavy loading with maximum intentional acceleration of the training load—and, to our knowledge, none of them in combination with a nutritional intervention. Further, none of the studies seemed to focus on optimizing the protein balance before starting the exercise all which contrasts with the present study.

Even though the current recommendation of total protein intake for older adults is ≥ 1.0 g protein/kg/day based on European recommendations [17], it has been suggested that older adults, and especially frail older people, can benefit from an even higher protein intake of 1.5 g protein/kg/day [18, 19]. To evaluate the effects of a higher intake in comparison with the current recommendation, we have included the REC group as one of the intervention arms (illustrated in Fig. 1).

